#### Hypotheses

There are four hypotheses relating to the primary objective:
(i)That an intervention offering 1 months of postpartum financial incentives will be significantly more effective for aiding smoking cessation up to 12 months postpartum than a no incentives condition.(ii)That an intervention offering 3 months of postpartum incentives will be significantly more effective for aiding smoking cessation up to 12 months postpartum than a no incentives condition.(iii)That an intervention offering 12 months of postpartum incentives will be significantly more effective for aiding smoking cessation up to 12 months postpartum than an intervention offering 3 months of postpartum incentives.(iv)That there will be a significant linear trend in smoking cessation across the three study groups, with rates of abstinence increasing from the no incentives group, to the 3 months incentives group, to the 12-month incentives group.

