#### Sample size {14}

We estimate that the proposed sample size of 900 women will give 90% power at an alpha threshold of 0.017 to detect a difference in abstinence rates across any two groups of 13.6% at 12-month follow-up. It is anticipated that the abstinence rate in the control group will be 9% at 12-month follow-up, that there will be 22.6% abstinence at 12 months follow-up in the 3-month incentives group and 36.2% abstinence at 12 months follow-up in the 12 months incentives group. The figure of 9% in the no incentives group is conservatively based on the assumption that over 90% of women without incentives may relapse by 12 months postpartum [3]. The estimate of 13.6% difference is based on the group difference found by Tappin and colleagues in a study of incentives during pregnancy [34]. The threshold for alpha is reduced to 0.017 to correct for multiplicity and allow comparisons across the three arms. This sample size will also give 100% power to detect a linear trend in abstinence across the three groups (*p* < 0.05) from control to 12-month intervention.

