### Statistical methods

#### Statistical methods for primary and secondary outcomes {20a}

The plan for statistical analysis is reported here in accordance with guidance for RCTS [35, 36].

We will use descriptive statistics to present the baseline characteristics of the three study groups. Descriptive statistics will also be used to report rates of recruitment, retention and follow-up at 3 months and 12 months postpartum and to report the numbers of women who relapsed before the birth vs after the birth, separately for the two study groups. Again, descriptive statistics will be used to present the following secondary outcomes at 3 and 12 months postpartum: use of nicotine products, smoking in the home, partner smoking status, use of additional smoking cessation support beyond that provided in the trial and use of the iCO (single-person use) monitor beyond that required for the research.

Analyses of smoking status, for primary and secondary outcomes, will be performed for the intention-to-treat population and reported in accordance with the Consolidated Standards of Reporting Trials (CONSORT) statement [37, 38], including all women who are randomised and meet the eligibility criteria. If ineligible persons are mistakenly randomised into the trial, the independent trial steering committee will review the case for removing the participant from the analysis, such that this decision is unbiased and not influenced by events that occurred after randomisation (and may therefore be affected by whether patients received experimental or control treatment) [39].

Women lost to follow-up will be presumed to have returned to smoking [19]. This assumption is standard in the smoking cessation literature as the pattern of missingness is not random. We will compare differences in smoking cessation outcomes between all three treatment groups, using logistic regression adjusted for the random effect of site (i.e. NHS Trust), with statistical significance determined by the likelihood-ratio test, and with pairwise comparisons between treatment groups in accordance with the study objectives, using a *p* value of 0.017 adjusted for the three comparisons. The estimate of effect will be given as the odds ratio and 95% confidence interval for each of the three comparisons. We will also look for a linear trend in smoking cessation across the three groups, by examining the significance (*p* < 0.05) of a linear contrast across the groups from control to 12-month intervention.

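### The linear-trend test is a primary hypothesis but sits at p < 0.05 outside the 0.017 correction; it largely repeats 12-month v no incentives and cannot alone show a stepwise rise

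*Protocol article*

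**What the plan says.** The section on hypotheses states: "There are four hypotheses relating to the primary objective". Three are pairwise. The fourth reads "That there will be a significant linear trend in smoking cessation across the three study groups", and goes on "with rates of abstinence increasing from the no incentives group, to the 3 months incentives group, to the 12-month incentives group".

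The sample size section explains the stricter level: "The threshold for alpha is reduced to 0.017 to correct for multiplicity and allow comparisons across the three arms". It then adds, at p < 0.05: "This sample size will also give 100% power to detect a linear trend in abstinence across the three groups".

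The statistical methods section {20a} repeats the split. Pairwise comparisons are made "using a *p* value of 0.017 adjusted for the three comparisons". The trend is examined separately, at p < 0.05, through the significance "of a linear contrast across the groups from control to 12-month intervention". No scores are given for the contrast. The section states no testing order and no gate for the trend, and does not call it supportive or exploratory. The trial status section again quotes the trend at p < 0.05, with 100% power at 154 per group.

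**The concern.** The article counts four primary hypotheses and corrects for three. The one left out is not a separate question. A linear contrast over three groups puts most or all of its weight on the two end groups, so it asks again, at a looser level, what 12-month v no incentives has already asked at 0.017.

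Two things are at stake. The first is error control: the four hypotheses together are not held at 5%, and one report could call 12-month v no incentives non-significant while calling the trend significant on almost the same evidence. The second is interpretation. Hypothesis (iv) also describes an ordering through the 3-month arm, and a contrast with little or no weight on that arm cannot carry it. That matters for a choice between a £120 and a £300 scheme, because the article expects only 60% power for 3 v 12 months but reports 100% for the trend.

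**Working it through.** **Inputs.** From the sample size section: pairwise level 0.017, trend level 0.05, assumed rates 9%, 22.6% and 36.2%, and 900 women (300 per group). From the trial status section: 154 per group. Assumed here: two-sided tests, and no site effect in the calculations. Hypothesis (i) is printed as 1 month; no such arm exists, so I read it as 12 months.

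**1. The article's own figures reproduce.** The formula is power = Φ{[d − z√(2p̄(1−p̄)/n)] / √([p₁(1−p₁)+p₂(1−p₂)]/n)}, with z = 2.387 for two-sided 0.017. For 22.6% v 36.2% and n = 300, p̄ = 0.294, the null standard error is 0.0372 and the alternative one 0.0368. Then (0.136 − 2.387 × 0.0372)/0.0368 ≈ 1.28, which is 90.0% power. At n = 154:

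| Comparison | Stated | Recomputed |
|---|---|---|
| 3-month v 12-month | 60% | 59.3% |
| None v 3-month | 82% | 81.6% |
| None v 12-month | 100% | 99.98% |

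**2. What the contrast is.** Equally spaced scores 0, 1, 2 centre to weights (−1, 0, +1). In a three-group logistic model that is log-odds(12-month) − log-odds(none), which is the pairwise contrast itself. Example: 14, 14 and 26 abstinent of 154. The log odds ratio is ln(26/128) − ln(14/140) = 0.709; its standard error is √(1/14 + 1/140 + 1/26 + 1/128) = 0.353; z = 2.01; p = 0.045. This Wald result is the same for the pairwise test and for the contrast: it fails at 0.017 and passes at 0.05.

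If group is entered as a numeric score 0/1/2 instead, the test is not identical (p = 0.035 here), but under the null the absolute statistics correlate above 0.996.

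Scores 0, 3, 12 (mean 5) give weights (−5, −2, 7). The correlation with (−1, 0, 1) is (5 + 7)/√(2 × (25 + 4 + 49)) = 12/√156 = 0.96.

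Ratio of levels: 0.05/0.017 = 2.94.

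**3. Family-wise error when no arm has any effect.**

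| Tests | Error |
|---|---|
| Three pairwise at 0.017 | 4.5% |
| Plus trend at 0.05, equal spacing | 7.3% |
| Plus trend at 0.05, scores 0/3/12 | 7.2% |
| Three pairwise, all at 0.05 (reference) | 12.2% |

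The first and last rows agree with the studentised range; the middle rows are from 4 million normal draws. Binomial simulation at 154 and 300 per group gives 7.3% to 7.4% with equal spacing.

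**4. How often the two verdicts disagree.** This is the chance that 12-month v none gives p between 0.017 and 0.05, at 154 per group and 9% in control. For a true difference of 8 points it is 17.5%; for 10 points, 16.3%. Those two differences are my assumptions. At the planned 27.2 points (36.2 − 9) it is about 0.01%.

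**5. Ordering (equal spacing, 154 per group).** With 14, 5 and 26 abstinent, the contrast has p = 0.045 although the 3-month arm lies below control (p = 0.041). With 14, 40 and 28, it has p = 0.022 although the 3-month arm is the highest.

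**The case against.** Several points on the other side are fair.

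- A reader might infer that the trend test undoes the 0.017 correction. It does not. None v 3-month and 3-month v 12-month stay at 0.017, and so does the pairwise verdict on 12-month v none. Error reaches about 7.3%, not the uncorrected 12.2%.
- A reader might infer that hypothesis (iv) is not tested at all. It names a linear trend, and a linear contrast tests that component. Only the ordering is beyond its reach.
- With true rates of 9%, 9% and 22.6% and 154 per group, the contrast is significant in about 92% of trials. That is not a false-positive rate, because a linear component is really present. The pairwise odds ratios reported alongside would show the 3-month arm level with control.
- Exact identity with 12-month v none needs equally spaced scores, which the article does not state. With 0/3/12 the 3-month weight is not zero.
- Section {20a} mentions a likelihood-ratio test of all three groups. If that were an overall test at 0.05 gating everything else, family-wise error would be about 4.7%. But the text states no gate, so this is only a possible reading.
- Conflicting verdicts are negligible under the planned effects; they arise only if the effects are much smaller.

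These points limit how strongly the concern can be put. They do not explain why one of four hypotheses under the primary objective has its own uncorrected level. Nor is this a detail left to a later analysis plan, since both thresholds are fixed in the article.

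**Conclusion.** The point holds in a limited form. One of the four hypotheses under the primary objective lies outside the multiplicity correction. Its test is the 12-month v no-incentives contrast, or a close relative of it, at 2.94 times the level set for that comparison. With no effect in any arm, family-wise error is about 7.3% (7.2% with scores 0/3/12) rather than 4.5%. This assumes two-sided tests and no overall gate.

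A significant trend supports a linear component. It does not by itself support a rise from none to 3 months and again from 3 to 12 months. The pairwise analyses are sound as planned, and nothing about the data or the sample size is affected.

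**What to change.** Change the wording in {20a} and in the analysis plan, which the article says will be agreed before the treatment code is broken:

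1. Test the trend at 0.017, or test it only after 12-month v no incentives is significant at 0.017, or label it supportive. With equal spacing, either of the first two leaves family-wise error at about 4.5%. With scores 0/3/12, the gate also gives 4.5% and the 0.017 level gives about 4.7%.
2. State the scores.
3. State that a significant trend alone does not establish a stepwise rise, and that the ordering is to be read from the two adjacent comparisons reported beside it. Do not require both to be significant. That would replace the trend hypothesis by (ii) and (iii) together, and at 154 per group both succeed in only about 45% of trials under the planned rates.

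The cost is a slightly stricter threshold for the trend. Under the planned rates at 154 per group, trend power is about 99.98% at 0.017, against 99.996% at 0.05. No data, participants or pairwise thresholds change.

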### Interim analyses {21b}

There will be no interim analyses.

### Methods for additional analyses (e.g. subgroup analyses) {20b}

We will conduct a secondary-analyses adjusting for key baseline maternal variables that are predicted to be related to smoking status (i.e. socio-economic status, cigarette consumption before pregnancy, depression and age) and type of smoking cessation service (midwife-led or not) [40]. We will also conduct sensitivity analysis to examine the effects of remote (i.e. during COVID-19) versus face-to-face consultations. We will also consider whether the women have been supported by a significant other.

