### Baseline measures

In a baseline questionnaire, administered by the SSS advisor before randomisation, we will assess measures which have been shown to predict postpartum smoking relapse [29] and which we would want to ensure are similar for the three study groups, as potential confounders of any effects on smoking cessation (see Table 1). These measures are:
AgeEthnicityHighest educational qualificationOccupationGestationLevel of cigarette consumption before pregnancyExpired CO level in ppmParity (i.e. number of previous pregnancies that have gone beyond 24 weeks)Assessment of any smoking in the home and of whether partner smokesLength of time since last smoking (months/weeks)Self-efficacy: rating of ‘How confident are you that you will continue not to smoke at least until your baby’s first birthday?’ (not at all confident, slightly confident, moderately confident, very confident, extremely confident) [30]Depression: Edinburgh Postnatal Depression Scale [31] (for the item **‘The thought of harming myself has occurred to me**’**, if women respond ‘Yes, quite often’ or ‘sometimes’, they will be referred to** their health visitor, family nurse partnership or GP)Breastfeeding intent [32]Alcohol consumption: Alcohol Use Disorders Identification-Consumption (AUDIT-C) test [33, 34]Use of support for smoking cessation beyond what is provided in the trialWhether they recruited a significant other supporter (SOS) during their pregnancyUse of nicotine replacement therapy (NRT) in the last week and main types of NRT usedUse of heat-not-burn products in the last weekUse of e-cigarettes in the last week

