All outcomes will be analysed collectively following the completion of the final follow-up at 12 months postpartum. A more detailed statistical analysis plan will be agreed to before the end of data entry and before the treatment code is broken.

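### A secondary objective asks whether maternal characteristics and service type change the effect of incentives, but the protocol plans only to adjust for them, which does not estimate this

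*Protocol article*

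**What the plan says.** The protocol article's Secondary objectives list four aims. The third is to identify what maternal characteristics (pre-pregnancy cigarette consumption is the example) and service type (midwife-led or not) do to the effectiveness of the intervention.

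These variables reappear in an analysis in one place only, Methods for additional analyses {20b}: "We will conduct a secondary-analyses adjusting for key baseline maternal variables that are predicted to be related to smoking status", listed as "socio-economic status, cigarette consumption before pregnancy, depression and age) and type of smoking cessation service (midwife-led or not". They are chosen because they are expected to predict smoking status. The Baseline measures section takes the same view and describes the baseline variables "as potential confounders of any effects on smoking cessation".

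The main model in Statistical methods {20a} compares the three arms "using logistic regression adjusted for the random effect of site (i.e. NHS Trust), with statistical significance determined by the likelihood-ratio test", followed by pairwise comparisons with an odds ratio and 95% confidence interval for each of the three. No interaction term, subgroup-specific effect or heterogeneity test is mentioned for any variable. The phrase about subgroup analyses in the {20b} heading belongs to the reporting-item title, and no subgroup analysis is described beneath it. The same section adds a sensitivity analysis of remote versus face-to-face consultations and a consideration of significant-other support. Neither concerns the variables in the objective.

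On further detail, {20a} says: "A more detailed statistical analysis plan will be agreed to before the end of data entry and before the treatment code is broken".

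**The concern.** The objective and the method answer different questions. The objective asks for whom, or in which kind of service, incentives work better. A model with arm and covariates as main effects assumes that the odds ratio for each arm comparison is the same at every level of each covariate. It can say that heavier smokers relapse more; it cannot say whether incentives help heavier smokers more or less than others.

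Two things are at stake. One of four secondary objectives would go unanswered if the text is followed. And a covariate coefficient reported against that objective could be misread as evidence about who benefits, when it describes only who stays abstinent.

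**Working it through.** **1. The plan's own figures, to fix the inputs.** Sample size {14} states "900 women will give 90% power at an alpha threshold of 0.017 to detect a difference in abstinence rates across any two groups of 13.6" percentage points. It assumes that "the abstinence rate in the control group will be 9% at 12-month follow-up", with "22.6% abstinence at 12 months follow-up in the 3-month incentives group and 36.2% abstinence at 12 months follow-up in the 12 months incentives group". The binding pair is 22.6% v 36.2%. With two-sided alpha 0.017 (z = 2.387), 90% power (z = 1.282) and mean rate 0.294:

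n = [2.387 × √(2 × 0.294 × 0.706) + 1.282 × √(0.226 × 0.774 + 0.362 × 0.638)]² / 0.136² ≈ 300 per arm, or 900 in total, as stated.

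At the 154 per arm expected under Trial status, the same method gives 59.3%, 81.6% and 100% power against the stated 60%, 82% and 100%. The sample-size figures are sound and are not the issue here.

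**2. What adjustment returns when the effect does and does not vary.** Take control v 3-month incentives (9% v 22.6% overall) and a binary covariate split 50:50 (an assumption). Fit arm + covariate by logistic regression to the expected counts.

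| Situation | Control rates, two halves | Intervention rates, two halves | True OR in each half | Fitted arm OR | Fitted covariate OR |
|---|---|---|---|---|---|
| A. Uniform effect, covariate irrelevant | 9%, 9% | 22.6%, 22.6% | 2.95, 2.95 | 2.95 | 1.00 |
| B. All benefit in one half | 9%, 9% | 9%, 36.2% | 1.0, 5.7 | 3.07 | 3.07 |
| C. Uniform effect, covariate purely prognostic | 4.7%, 13.3% | 13.3%, 31.9% | 3.07, 3.07 | 3.07 | 3.07 |

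The arm odds ratio hardly moves between A and B. The covariate coefficient does move, but B and C give the same fitted model. The rates in C are the fitted rates from B, and they have the same arm totals (9% and 22.6%) and the same covariate totals. In B the covariate decides who benefits; in C it has nothing to do with who benefits. The planned output does not tell them apart.

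**3. What an interaction estimate would look like.** For one arm comparison with n per arm,

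Var(log OR) = 1/[n p₁(1 − p₁)] + 1/[n p₂(1 − p₂)].

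With equal halves and the same rates in both (assumptions), each half has twice this variance. The difference of the two log odds ratios then has four times it, so SE(interaction) = 2 × SE(log OR). The 95% interval runs from the estimate divided by, to the estimate multiplied by, exp(1.96 × SE). At n = 154:

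| Comparison | Var(log OR) | SE | Interaction SE | Factor either way |
|---|---|---|---|---|
| Control v 12-month (9%, 36.2%) | 0.0793 + 0.0281 = 0.107 | 0.328 | 0.655 | 3.6 |
| Control v 3-month (9%, 22.6%) | 0.0793 + 0.0371 = 0.116 | 0.341 | 0.682 | 3.8 |
| 3-month v 12-month (22.6%, 36.2%) | 0.0371 + 0.0281 = 0.065 | 0.255 | 0.511 | 2.7 |

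**4. Power of such an interaction.** For control v 3-month, two-sided 0.05 and a 50:50 split, a Wald test has 9%, 17% and 35% power at 154 per arm for a ratio of odds ratios of 1.5, 2 and 3. At 300 per arm it has 13%, 29% and 60%. The documents give neither the splits nor the sizes of any modification, so these values are illustrative. The calculations in steps 2 to 4 also ignore the random site effect.

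**The case against.** The strongest reply is that this is a journal article, that a fuller analysis plan is promised before the treatment code is broken, and that interaction terms are the kind of detail such a plan supplies. The article does not say that adjustment is the only analysis for this objective, nor does it link {20b} to the objective by name. Part of this stands: nothing prevents the analysis plan from adding interactions, and silence alone would be no finding. But the article is not silent. It takes the variables in the objective and names a method for them, and that method addresses another question. An analysis plan that merely elaborates {20b} would carry the mismatch forward.

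It is also fair to say that the interactions will be weak. With three arms, each binary variable brings two interaction parameters, so five variables bring at least ten imprecise estimates. That is a reason to call them exploratory and to offer rewording of the objective as an alternative. It does not make adjustment answer the question.

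A reader might infer more than the text supports on two points:

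- **Service type and site.** With four Trusts, one might state that service type is a property of the Trust and therefore confounded with site. Study setting says that the sites have different service configurations, including midwifery-led and advisor-led ones. It does not say that each Trust has only one type. If a Trust has both, a within-Trust contrast exists.
- **A single figure.** The adjusted model does not collapse the trial to one treatment odds ratio, because {20a} plans one for each of three comparisons. Likewise the factor of 3.6 belongs to control v 12-month only.

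**Conclusion.** The mismatch is real. The third secondary objective is about effect modification. The analysis named for its variables is covariate adjustment, which estimates an overall odds ratio for each arm comparison and prognostic coefficients, but no difference in effect. This follows from the form of the model and does not depend on sample size.

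The matter is moderate. The primary outcome, model, alpha and sample size are untouched. The maternal variables are baseline measures, so the gap can be closed before unblinding. The size of the problem is one of four secondary objectives left without an estimate. What the remedy can deliver is limited: interaction intervals spanning a factor of about 2.7 to 3.8 either way at 154 per arm. Those figures rest on the plan's assumed abstinence rates, a 50:50 split and equal rates in both halves; a less even split would generally widen them. Whether service type can be separated from site is open on these documents.

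**What to change.** In {20b} and in the analysis plan, before the treatment code is broken:

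1. Add arm-by-variable interaction terms, one variable at a time, for socio-economic status, pre-pregnancy cigarette consumption, depression, age and service type, with the coding of each fixed in advance.
2. Report interaction odds ratios with 95% confidence intervals and the abstinence rate in each arm by subgroup. Label all of this exploratory.
3. Keep the covariate-adjusted model, described as a separate analysis of the overall effect.
4. Check whether service type varies within Trusts. If it does not, report that its interaction cannot be separated from other differences between the four sites.

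If the investigators do not want interaction analyses, reword the secondary objective so that it asks for the effect of incentives adjusted for these variables. Either route restores consistency.

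The cost is a short change of wording and a few low-power models. The maternal variables are already collected at baseline, and service type should be obtainable from the recruiting service. No change to recruitment, follow-up or the primary analysis is needed.
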